**Fig 2 pone.0272481.g002:**
[figure not shown]
Flowchart of non-beneficiary (non-BFP) and beneficiary of the Bolsa Familia Program (BFP) to test the association between BFP and youth mental health-related hospitalizations and suicide.

**Table 1 pone.0272481.t001:** Summary of the dataset’s description, from 2001 to 2018.

Dataset	Description	Sample	Variables of interest
The 100 Million Brazilian Cohort Baseline^70,73^	It was built from socioeconomic and demographic information of individuals applying for social benefits in Cadastro Unico (CadÚnico). CadÚnico is an extensive questionnaire with information on the household and on each individual.	114 million Brazilian cohort, including 66,079,181 Bolsa Familia Program beneficiaries and 47,928,524 non-beneficiaries. Among them 41,764,126, youth aged from 5–24 years old in the day of registration.	Demographic and socioeconomic variables (sex, age, ethnicity, education, work), conditions of the household (type of residence, material of household, household density, household supply, garbage destination etc), Health Care utilization, Institutional and community support (participation in groups, access to Social Assistance Reference Center, etc.) and Brazilian government social protection programs (BFP, etc).
Mortality Information System (SIM)^74,75,72^	The national system aimed to collect information on all deaths in Brazil death certificates. All deaths are recorded using a national standardized form and causes of death are registered according to the updated International Classification of Diseases CID-10.	All mortality cause (n = 21,313,290), including suicide (n = 181,527).	Demographic and socioeconomic variables (sex, age, ethnicity, education, work), place the death took place and primary and secondaries causes of death.
Hospital Information System (SIHSUS)^1^	All hospitalizations admissions financed by the Brazilian National Health System are recorded in this system. It includes about 80% of the Brazilian populations, approximately 150 million people	Hospitalizations from mental illness 5,478,980, including: 1,698,663 from alcohol and substance use-related disorders; 1,952,605 from schizophrenia; 832,974 due mood disorders, etc.	Identification and qualification of the patient, procedures, examinations, and medical acts performed, diagnosis, reasons for discharge, amounts due etc.
Notifiable Diseases Information System (SINAN)	This dataset comprises compulsory notifiable diseases information and violence, emotional and physical, as well as suicide attempt.	Compulsory notifiable diseases, including occurrences reported for: self-inflicted violence (333,933), interpersonal violence (2,111,051), and intimate partner violence (433,664).	Individual sociodemographic and clinical data of suspected and confirmed cases of interpersonal and self-inflicted violence (suicide attempt and self-agression) and intimate partner violence. It also includes information regarding the perpetrator, such as relationship with the victim.
Demographic Census (IBGE)	Household census to collect information on all households and individuals in the country and characterize the Brazilian population in terms of its demography and socioeconomic characteristics.	All Brazilian municipalities (n = 5,670).	Population, fertility, mortality, migration, housing characteristics, characteristics of the neighbourhood, education, income, labour, social inequality (Gini index), Human Development Index (HDI), proportion of poor people, etc.

Besides information from BFP, from the CadÚnico, we will also access information from the Hospitalization Information System to identify hospitalizations from: (A) mood disorders (832,974); (B) anxiety; (C) psychosis (1,952,605); (D) prescribed or illicit drug abuse and dependence; (E) alcohol abuse and dependence; (F) alcohol-related liver, problem/chronic liver disease; (G) physical injuries (228,278); (H) attempted suicide (178,606); and (I) suicide (181,527), from 2001–2018. As well as violence notifications from the Brazilian Notification System for Health Surveillance and all cause-specific mortality data, collected from the Brazilian Mortality Information System. All hospitalization, notification, and mortality information data were obtained from the DATASUS held by the Brazilian Ministry of Health and transferred to CIDACS [29] for research purposes. All the data are recorded in the three systems using the International Classification of Diseases, 10th revision. Information systems have improved considerably in Brazil; an analysis of the adequacy of mortality data from 2003 to 2005 found high quality and reliable information [30]. All the data available at CIDACS/FIOCRUZ covers a period from 2001–2018; however, we may access more recent years when the study begins.

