## Materials and methods

### Conceptual framework

There is a strong association between poverty and poor mental health in young people [17, 18]. Psychiatric disorders in youth are often associated with social problems such as school failure or delinquency, which increase the risk of poverty and other adverse outcomes into adulthood [3, 5]. Furthermore, mental health support is inequitably distributed, so that people living in poverty and those facing other vulnerabilities are at higher risk [5]. Therefore, youth living in LMICs have increased vulnerability to mental illness and associated high mortality rates due to their social and environmental situations [11, 19].

Economic hardship can affect mental health, increase stress, and decrease self-esteem [20]. Economic stressors have been estimated to account for 24% of suicide occurrence [21]. Income inequality is associated with increased suicide rates for both men and women, mechanisms by which this association exists include limited access to resources and increased sense of injustice for not achieving as much economic success as other people [21]. Some studies indicate that poverty is more frustrating in more unequal communities, possibly because individuals become frustrated when comparing themselves to others [22]. In Brazil, income inequality has been associated with higher suicide rates [8] Poverty can increase predisposition to mental illness such as alcohol abuse/dependence and depression in families [22]. It has been shown that cash transfer programs can improve general mental health [23] and increase hope and optimism [24]. It can also reduce factors that are associated with suicide, such as exposure to violence and impulsivity. Factors that can be tested in the current project by accessing notifications and hospitalizations related to those causes.

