**Fig 1 pone.0272481.g001:**
[figure not shown]
Potential mechanisms and pathways through which Bolsa Familia Program (BFP) may affect mental health-related hospitalizations and suicide among children and youth.

Therefore, the main potential mechanisms this project will test, through which BFP may be associated with better mental health outcomes are: (i) by reducing parental mental illnesses and family separations; (ii) by improving school retention (BFP has conditionalities related to education and health); (iii) by reducing exposure to violence; and finally, (iv) by decreasing impulsivity (Fig 1).

This protocol offers a unique opportunity to test these mechanisms in a countrywide dataset, and allows subgroup analyses. Considering that the impact of those factors may happen differently among more vulnerable groups, such as black youth, women, youth with lower income and living in deprived areas, after examining the impact of cash transfers on interrupting the pathways between poverty and poor mental health through one or more mechanisms previously mentioned (e.g., improving educational outcomes, reducing impulsivity, etc). We will then evaluate the differential impact of BFP across race and gender, and how this might be explained by the mechanisms. If the effect of the cash transfer is stronger among minorities, decreasing inequalities, it can also be one of the mechanisms through which this program may improve youth mental health.

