#### Linkage of the databases

To test the pathways and mechanisms of a cash transfer program on youth mental health, we will integrate the five large individual datasets, previously mentioned, with aggregate data, analyzing the variables previously described. We have previously precisely linked the BFP data to the 100 Million Brazilian Cohort, using a social identification number (NIS). Individuals who have died by suicide, hospitalized by suicide attempt or mental disorders, or were a victim of violence (self-inflicted or interpersonal), were identified by linking Brazilian Mortality Information System (SIM), Hospitalization Information System (SIH), Notifiable Diseases Information System (SINAN) data, respectively with the 100 Million Brazilian Cohort. The 100 Million Brazilian Cohort and Health databases were linked by the Center for Data and Knowledge Integration for Health (CIDACS) [1], using Record Linkage software which was developed by CIDACS [26, 28, 31].

The linkage algorithm used five variables to identify matching records from the two databases (SIM and CadÚnico), each of which was recorded in all the datasets being linked: the beneficiary’s name, mother’s name, sex, municipality of residence code, and date of birth. The Record Linkage software performed two main steps: The record that corresponded to the data of each 100 Million Brazilian Cohort individual (the larger dataset) was indexed in the Lucene Apache library, which has a method of indexing files and performed a search of data in these files. Then for each information in the health dataset, the algorithm searched the indexed database of the 100 Million Brazilian Cohort for a potential match. A similarity calculation was performed for these records, generating a score indicating the similarities between the two linked records. The similarity calculation was performed and generated a “weighted average” which is the value of the similarity score. Finally, if the score was equal to or greater than 0.95, the link was accepted (as a correct link). In order to check the entire linked dataset, robust accuracy tests were performed, to assess the overall linkage quality. Analysis of linkage accuracy included manual verification and assessing the Receiver Operating Characteristic (ROC) curve. Details were reported elsewhere [26].

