We will apply methods from the SEM group, to specify and test the paths laid out in Fig 1. SEM will be used to fit models to the specifications in Fig 1 to allow a judgement on which models best fit our data, therefore allowing the identification of the model, which might be the closest to the causal paths underlying the relationship between exposure and outcome, including potential confounders. Estimation is performed either by Maximum Likelihood. Besides identification of the best fitting models, SEM allows detailing the relationship between indicators (variables) included in the models. After deciding which models are optimal, the particular coefficient estimates are calculated, which can be of fundamental importance to the identification of the intermediate nodes that have the highest influence on the outcome, or which act as mediators or moderators. Mediators are useful representations of confounders, and as long as the path coefficients are calculated, one can precisely estimate the effects resulting from the mediator.

Aim 4: Investigate early life exposures, intergenerational aspects, and to forecast scenarios in Brazil until 2030 using microsimulation models.

Finally, to match this aim we will examine: timing of the intervention in the life course, e.g., if cash transfer delivered earlier in life (e.g., in 2004 when an adolescent was 14 years old) will be associated with lower mental health-related hospitalizations and lower suicide rates 10 years later (when the same adolescent will be 24 years old); and whether mental health-related problems such as suicidality, post-traumatic stress disorder (PTSD), violent behavior passes over to second generations; and, furthermore to forecast scenarios of mental health-related hospitalizations and suicide rates using microsimulation models. This will leverage the results from previous objectives and compare the impact of different BFP implementations on mental health-related hospitalizations and suicide in Brazil until 2030.

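### Exposure to violence (mechanism iii) rests mainly on notified victims, and being notified may itself depend on Bolsa Família; Aim 4 assigns no variable to violent behavior

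*Protocol article*

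**What the plan says.** The Conceptual framework lists four mechanisms to be tested; the last two are given as "iii) by reducing exposure to violence; and finally, (iv) by decreasing impulsivity". Of exposure to violence and impulsivity together it says: "Factors that can be tested in the current project by accessing notifications and hospitalizations related to those causes".

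Data and measures lists hospital admissions by cause and then adds "As well as violence notifications from the Brazilian Notification System for Health Surveillance". In Table 1 the SINAN row describes "suspected and confirmed cases of interpersonal and self-inflicted violence" and says that some perpetrator information is held, with the relationship to the victim as an example. Linkage of the databases describes the SINAN link as finding cohort members who "were a victim of violence (self-inflicted or interpersonal").

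On the exposure side, the Conceptual framework notes that "BFP has conditionalities related to education and health", and Data and measures gives access to public services as one of the programme's three aims.

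The Discussion acknowledges a proxy for one mechanism only, physical injuries for impulsivity. In the same paragraph it says that both will be controlled for health care access, so large differences between groups are unlikely. It is not clear what "both" refers to.

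Under Aim 4, the Analytic strategy asks, among other problems, whether "violent behavior passes over to second generations". The intergenerational model that follows has the child's mental health variable as its outcome.

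**The concern.** A notification is a recorded event, not the violence itself: someone has to suspect or confirm a case and report it. If receiving BFP brings children into more contact with schools and health services, the programme can change two things at once, the violence and the probability that it is recorded. The two changes would push the notification rate in opposite directions.

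A real protective pathway could then look weak, absent or harmful. Table 1 counts over two million interpersonal violence notifications, so sampling error is unlikely to mask such a bias; it could be reported as a precise effect. The structural equation models would carry it into the indirect effect.

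Aim 4 has a separate gap. A question about violent behavior cannot be answered from records that identify victims unless the plan says which field stands for the behavior. If victimization were used without saying so, the conclusion would go beyond the data.

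**Working it through.** **Is there a figure to reproduce?** No. The article gives no effect size, power or notification rate by BFP status for this mechanism. The arithmetic below uses assumed values to show what the bias would take.

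**Formula.** Observed notification ratio (BFP vs non-BFP) = true violence ratio × detection ratio. Detection ratio means the probability that violence is notified in BFP families divided by the same probability in non-BFP families. The estimate reaches the null when the detection ratio equals 1 / true ratio, and the sign reverses above that.

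**Illustration for a true ratio of 0.90 (assumed).**
- Notification probability rises from 10% to 11%: 0.90 × (0.11/0.10) = 0.90 × 1.10 = 0.99, almost no visible effect.
- Notification probability rises from 10% to 12%: 0.90 × (0.12/0.10) = 0.90 × 1.20 = 1.08, reversed sign.
- Break-even: 1/0.90 = 1.11.

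**Range (all values assumed).** The cells are observed ratios.

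| True ratio | Break-even detection ratio | Detection 1.0 | 1.1 | 1.25 | 1.5 | 2.0 |
|---|---|---|---|---|---|---|
| 0.95 | 1.05 | 0.95 | 1.05 | 1.19 | 1.43 | 1.90 |
| 0.90 | 1.11 | 0.90 | 0.99 | 1.13 | 1.35 | 1.80 |
| 0.80 | 1.25 | 0.80 | 0.88 | 1.00 | 1.20 | 1.60 |
| 0.70 | 1.43 | 0.70 | 0.77 | 0.88 | 1.05 | 1.40 |
| 0.50 | 2.00 | 0.50 | 0.55 | 0.63 | 0.75 | 1.00 |

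Reversal needs detection to rise by proportionally more than violence falls. Smaller differences only attenuate. The smaller the true effect, the less it takes.

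**Do the planned methods remove this?**
- *Aim 1 regressions* adjust for mental health care access, not for general service or school contact.
- *Propensity score matching* lists demographic, income and housing variables and previous psychiatric hospitalization, but no service-contact variable. Table 1 does list health care utilization and access to a social assistance centre in the cohort baseline, but a baseline value cannot capture contact that the programme adds later.
- *Aims 2 and 3* add mental health supply at municipality level only.
- *Regression discontinuity* compares families near the eligibility threshold. Receipt of BFP changes there, and any contact it brings changes with it, so a jump in notifications would mix violence with detection.
- *Agreement between matching and discontinuity*, which the plan treats as evidence of robustness, does not test this. Both methods deal with selection into BFP, and both use the same outcome records.

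**Aim 4, passages side by side.** The aim names violent behavior; the linkage finds victims; the modelled outcome is the child's mental health variable; SINAN holds some perpetrator information. Parent-to-child violence is therefore partly recoverable. A youth's own violence towards others has no described measure.

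**The case against.** The strongest reply is that the plan does not rely on notifications alone. The Conceptual framework mentions hospitalizations beside notifications, and cause-specific mortality is among the data. That is correct, and it makes the remedy consistent with the plan. But the sentence covers violence and impulsivity together, injury admissions are then assigned to impulsivity, and the list of admission causes has no assault category of its own. Notifications remain the only measure clearly assigned to mechanism (iii).

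Second, a reader might infer that notifications do rise with BFP contact, or that the sign will reverse. The documents do not support this. They give no notification rate by contact or BFP status and do not describe who notifies. The dependence is an inference from the programme's conditions and aims, and reversal is conditional.

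Third, adjusting for contact could help. It could reduce the ascertainment path, though imperfectly, because violence can itself cause contact. The difficulty is that the listed variables do not measure contact after enrolment.

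Fourth, a reader might conclude that violent behavior has no measure at all. That is too strong: Table 1 offers the relationship to the victim as an example of perpetrator information, not as its limit.

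Finally, assault admissions and homicides are no gold standard. The hospital system (SIH) records only admissions financed by the national health system, so it too depends on access. Severe events also leave out emotional and non-admitted violence. This stands, and it is why they should run beside SINAN rather than replace it.

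**Conclusion.** The point holds as a risk of differential ascertainment that the plan neither acknowledges nor controls. It should be dealt with before the mechanism analyses are run. Its size cannot be estimated from the documents. Under assumed values, a rise in detection of about 11% hides a 10% true fall in violence, a rise of 25% hides a 20% fall, and larger rises reverse the sign. If detection did not differ by BFP status there would be no bias from this source. If it were lower among beneficiaries, the bias would run the other way and exaggerate a benefit.

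For Aim 4 the conclusion is narrower: violent behavior has no assigned variable, and the described linkage supports statements about victims and, in part, about parents as perpetrators. The plan does not say that victimization will stand in for behavior; it leaves the matter open.

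**What to change.** **Mechanism (iii).**
1. Keep SINAN interpersonal notifications, and report confirmed cases separately from suspected ones.
2. Require a parallel measure: assault-coded hospital admissions (SIH) of the youth or a registered family member, and homicide deaths in the registered family from the mortality system (SIM).
3. Show the notification result over a stated range of detection ratios, for example 1.0 to 2.0, dividing the observed ratio by each (1.08 / 1.20 = 0.90).
4. State in advance that notifications alone will not support a conclusion that BFP raises violence, or that the mechanism is absent, when the less contact-dependent measures disagree.
5. Add differential notification to the limitations, and say what the Discussion's control for health care access covers.

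**Aim 4.** Restrict the claim to notified victimization, and to parent-to-child violence where the SINAN perpetrator field identifies the parent. Do not report transmission of violent behavior by the youth.

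**Cost.** Mostly coding and wording. The sources are already in the plan, but the SIH and SIM linkage is described for mental health and suicide events, so assaults and homicides may need further extraction. The parallel measure has fewer and more severe events, omits emotional violence and still depends partly on access.

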#### Linkage of the databases

To test the pathways and mechanisms of a cash transfer program on youth mental health, we will integrate the five large individual datasets, previously mentioned, with aggregate data, analyzing the variables previously described. We have previously precisely linked the BFP data to the 100 Million Brazilian Cohort, using a social identification number (NIS). Individuals who have died by suicide, hospitalized by suicide attempt or mental disorders, or were a victim of violence (self-inflicted or interpersonal), were identified by linking Brazilian Mortality Information System (SIM), Hospitalization Information System (SIH), Notifiable Diseases Information System (SINAN) data, respectively with the 100 Million Brazilian Cohort. The 100 Million Brazilian Cohort and Health databases were linked by the Center for Data and Knowledge Integration for Health (CIDACS) [1], using Record Linkage software which was developed by CIDACS [26, 28, 31].

The linkage algorithm used five variables to identify matching records from the two databases (SIM and CadÚnico), each of which was recorded in all the datasets being linked: the beneficiary’s name, mother’s name, sex, municipality of residence code, and date of birth. The Record Linkage software performed two main steps: The record that corresponded to the data of each 100 Million Brazilian Cohort individual (the larger dataset) was indexed in the Lucene Apache library, which has a method of indexing files and performed a search of data in these files. Then for each information in the health dataset, the algorithm searched the indexed database of the 100 Million Brazilian Cohort for a potential match. A similarity calculation was performed for these records, generating a score indicating the similarities between the two linked records. The similarity calculation was performed and generated a “weighted average” which is the value of the similarity score. Finally, if the score was equal to or greater than 0.95, the link was accepted (as a correct link). In order to check the entire linked dataset, robust accuracy tests were performed, to assess the overall linkage quality. Analysis of linkage accuracy included manual verification and assessing the Receiver Operating Characteristic (ROC) curve. Details were reported elsewhere [26].

